## Expected Results

According to our hypothesis, the experimental single-session bilateral TP NF protocol (enhancing left β/θ and reducing right β/θ) would restore the typical reading-related inter-hemispheric imbalance in adults with DD. Accordingly, we expect to find an enhanced left β/θ power ratio and a concurrent reduced right β/θ power ratio during the performance of linguistic tasks after the active NF training. Conversely, we expect the control group (i.e., placebo NF training) to maintain an abnormal activation of TP regions during the linguistic tasks (i.e., reduced left β/θ and enhanced right β/θ) and no modulation of the β/θ power ratio after training. In summary, we expect a significant Phase (pre vs. post) × Condition (active NF vs. placebo NF) interaction effect on the modulation of bilateral TP imbalance. Also, we expect these improvements to be greater for those participants with larger asymmetry scores as assessed in the screening phase.

As for the behavioral measures (i.e., reading, RAN, and verbal WM), despite previous evidence on cognitive enhancement after a single-session NF (e.g., Escolano et al., 2014), we did not formulate a specific hypothesis, but instead, we opted for an exploratory approach, due to the potential limited effect size of a novel single-session NF protocol in DD.

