To the best of our knowledge, despite the significant results obtained in previous NF research, no study has investigated a bilateral NF intervention targeting TP activation. The conjunction effect of the left increased and right decreased TP activation was found to be effective in NIBS interventions for Turkeltaub et al. (2012); Costanzo et al. (2016a, b); Younger et al. (2016).

Our hypothesis is to induce a reading performance improvement using bilateral NF to restore the typical TP hemispheric imbalance in the brain (Shaywitz et al., 1998; Sarkari et al., 2002; Eden et al., 2004; Simos et al., 2007; Rimrodt et al., 2009). As compared to NIBS, NF has fewer exclusion criteria and limitations in its application and could be safely applied in pediatric populations.

The present study protocol was designed to test the effect of a single-session bilateral NF protocol aimed at increasing the β/θ ratio in left TP areas and decreasing the β/θ ratio in the contralateral area on bilateral TP hemispheric imbalance during linguistic tasks in adults with DD. The second purpose of the study is to explore whether and to what extent the degree of asymmetry in the β/θ ratio can influence the outcomes of the training. Finally, the study aims at exploring the effect of the novel NF protocol on the reading and phonological skills of participants.

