### Neurophysiological Measures

EEG cortical activity will be recorded using the ProComp5 Infiniti System paired with the BioGraph Infiniti Software (Thought Technology Ltd.) from two active sites placed in TP7 and TP8, according to the International 10–10 system (Nuwer et al., 1998). Two reference electrodes will be placed on the earlobes and two ground electrodes will be placed on the mastoids. The sampling rate will be set at 256 Hz and impedance will be kept below 5 kΩ. Artifact rejection will be performed using both an amplitude threshold (20 μV) and visual inspection.

During the screening session, a measure of hemispheric asymmetry will be calculated by subtracting the right β/θ power ratio from the left β/θ power ratio at TP (i.e., TP7–TP8).

For the NF session, the separate power of the α frequency (8–12 Hz), the δ frequency (1–3 Hz), along with that of the target frequencies (β: 13–21 Hz; θ: 4–8 Hz) and their ratio (β/θ) will be extracted by the BioGraph Infiniti Software and will be considered for the analyses. Pre and post-training EEG recordings will include three phases: (1) resting-state with eyes open for 3 min; (2) a computerized phonological task, in which participants are required to decide whether a list of bi-syllabic word pairs rhymed or not (Spironelli et al., 2006, 2008); and (3) a computerized semantic task, in which participants are required to decide whether bi-syllabic word pairs from a list were semantically related or not. For a detailed description of the linguistic tasks, see Spironelli et al. (2006, 2008). For phases (2) and (3), both response times and accuracy rates will be recorded.

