### Data Analyses

First, demographics and behavioral baseline assessment of experimental and control groups will be compared, to test any potential difference between groups for variables relevant to the aim of the study, together with the variables related to the asymmetry scores as described in section “Procedure”. Thereafter, a series of GLMs is intended to be carried out to compare the effect of the active NF training with those of the sham NF training. For doing that, a mixed factorial ANOVA 2 × 2, considering Phase (pre vs. post) and Condition (experimental vs. sham) as the independent variables will be carried out for each dependent measure (i.e., separate left and right β and θ frequencies power during the linguistic tasks; left β/θ and right β/θ EEG power in resting state and during the linguistic tasks; accuracy and reaction times during the linguistic tasks, reading task, and RAN; accuracy in the digit span task). A correction for multiple comparisons will be applied (i.e., the Bonferroni correction). A sample size of 40 was calculated to be enough to achieve a statistical power of 0.87, for medium effect size (η^2^ = 0.06), by setting alpha at 0.05, in the GLMs we planned to carry out to test the effectiveness of the NF intervention.

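### The stated 2 × 2 model has no term for screening asymmetry, so it cannot answer the study's second purpose, and the predicted direction is ambiguous because the score is signed

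*Protocol article*

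**What the plan says.** The end of the Introduction (Dyslexia and Neurofeedback) gives as the study's second purpose to "explore whether and to what extent the degree of asymmetry in the β/θ ratio can influence the outcomes of the training". Procedure repeats this as one of two reasons for computing the score. The other is allocation, since randomization is stratified on the β/θ asymmetry scores.

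Neurophysiological Measures defines the score by "subtracting the right β/θ power ratio from the left β/θ power ratio at TP", that is, TP7–TP8.

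Expected Results describes the abnormal pattern during the linguistic tasks as "reduced left β/θ and enhanced right β/θ". After active training it expects an "enhanced left β/θ power ratio and a concurrent reduced right β/θ power ratio during the performance of linguistic tasks". It then adds the moderator expectation: "we expect these improvements to be greater for those participants with larger asymmetry scores as assessed in the screening phase".

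Data Analyses specifies a mixed 2 × 2 ANOVA for each dependent measure, "considering Phase (pre vs. post) and Condition (experimental vs. sham) as the independent variables". Asymmetry is mentioned there only among the variables compared between groups at baseline. Left and right β/θ are listed as separate dependent measures, and no left-minus-right imbalance outcome is listed.

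**The concern.** There are two difficulties.

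First, a declared purpose with a directional expectation has no analysis that could answer it. A baseline comparison of asymmetry between the arms shows whether allocation balanced the score. It says nothing about whether the training effect varies with the score. If no term is fixed in advance, a median split, a correlation in the active arm or a covariate model could each be presented later as the answer. A correlation within the active arm alone would not separate moderation of the training effect from change that would have occurred under sham. The variable used to stratify randomization is also absent from the model.

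Second, the phrase about larger scores can be read in two ways that lead to opposite predictions for participants with the abnormal pattern. Unless the reading is fixed, a slope of either sign could be offered as support.

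**Working it through.** **1. The plan's own figure, and what it covers.** Inputs from Data Analyses: N = 40, η² = 0.06, alpha 0.05, power 0.87. The pre-post correlation ρ is not given, so ρ = 0.5 is an assumption here.

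- f² = 0.06/0.94 = 0.0638, so f = 0.2526.
- Phase × Condition interaction with m = 2 measurements: λ = N·m·f²/(1 − ρ) = 40 × 2 × 0.0638/0.5 = 10.2, on 1 and 38 df.
- Power from the noncentral F is 0.876, or 0.869 with f rounded to 0.25. This reproduces 0.87.
- Other correlations do not reproduce it: ρ = 0 gives 0.60, 0.3 gives 0.75 and 0.7 gives 0.98.

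The 0.87 therefore matches the Phase × Condition interaction, which is a different test from the moderator question.

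**2. What the stated model can estimate.** The 2 × 2 model contains Phase, Condition and Phase × Condition. Write S for the screening score, C for condition and Δ for post minus pre. The moderator question concerns b₃ in

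Δ = b₀ + b₁C + b₂S + b₃(C × S).

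Here b₃ is the active-minus-sham difference in slope on S. In the repeated-measures layout it is the Phase × Condition × S term. The stated model omits both S terms, so b₃ is not estimated. Adding only Condition × S to the repeated-measures model would not be enough, because that term concerns the level averaged over pre and post.

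**3. Direction of the score.** S = left β/θ − right β/θ. With invented values for illustration:

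| Participant | Left | Right | Signed S | Absolute S |
|---|---|---|---|---|
| Abnormal pattern | 1.0 | 1.4 | −0.4 | 0.4 |
| Opposite pattern | 1.4 | 1.0 | +0.4 | 0.4 |

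On the signed scale, the larger score belongs to the participant already nearer the training target. On the absolute scale the two participants cannot be told apart.

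Whether a larger absolute score marks a more abnormal participant depends on where the sample lies. Take the deficit as −S and assume normally distributed scores:

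| Mean of S (in SD) | Correlation of signed S with deficit | Correlation of absolute S with deficit |
|---|---|---|
| −2 | −1 | +0.99 |
| −1 | −1 | +0.85 |
| −0.5 | −1 | +0.57 |
| 0 | −1 | 0.00 |
| +0.5 | −1 | −0.57 |

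The −1 follows by construction. The documents give no distribution of S, so the row that applies is unknown.

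**4. What a moderator test could deliver.** Adding S and C × S leaves 1 and 36 df. At alpha 0.05, N = 40 and ρ = 0.5 (assumed):

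- Moderator effect as large as the planning effect (f = 0.253): power 0.875. For ρ from 0.3 to 0.7 the range is 0.75 to 0.98.
- Half that f: λ = 40 × 2 × 0.01596/0.5 = 2.55, power 0.34. For ρ from 0.3 to 0.7 the range is 0.26 to 0.52.
- η² = 0.06 read as the partial η² of the moderator term itself: λ = 40 × 0.0638 = 2.55, power 0.34.

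**The case against.** A reader might infer that the prediction has the wrong sign. The documents do not support that. It would require both that larger is meant on the signed scale and that the authors expect more abnormal participants to gain more, and no section says either. The wording about degree in the Introduction and Procedure can naturally mean magnitude. If most participants share the pattern in Expected Results, a larger absolute asymmetry does mark a more abnormal participant (correlation +0.85 to +0.99 at mean scores of −1 to −2 SD). Even on the signed scale, the idea that participants nearer the target respond better is a possible hypothesis. In addition, the abnormal pattern is described for the linguistic tasks, while screening records both rest and tasks and the article does not say which recording yields the score. What remains is ambiguity about direction.

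A second inference would be that opposite patterns are placed in one stratum. That follows only if absolute values are used, and the text as written gives the signed difference.

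On the missing term, it can be argued that the ANOVA is introduced as the efficacy comparison, that the aim is exploratory, and that a condensed article may leave such a model to an analysis plan. This has some force for severity. It does not remove the point: the article itself names the model and its factors and assigns asymmetry a role in the analysis. That role is a baseline comparison, which cannot serve the second purpose. Nor do the documents show that the authors intend to rely on within-arm correlations. None are mentioned, and a general linear model can take a covariate.

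**Conclusion.** The point holds in two parts. The analysis as written cannot test whether screening asymmetry modifies the training effect, although this is the study's second purpose and carries a directional expectation. This part needs no numerical assumption, because it follows from the factors listed. The expectation itself is ambiguous: on the signed definition a larger score means less of the abnormal pattern, and on an absolute reading opposite patterns are merged.

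The consequence is limited to the moderator aim. The main Phase × Condition comparison stands, and its 0.87 reproduces if ρ = 0.5 is assumed. That figure should not be read as covering moderation, where power could be about 0.34 at half the planning f under the same assumption. The correction is worthwhile and cheap, but the trial's main conclusion does not depend on it.

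**What to change.** - State that the signed TP7–TP8 score is used for both stratification and analysis.
- Word the expectation on that scale. The authors must say which direction they mean. If they mean that more abnormal participants gain more, the prediction is a greater active-minus-sham effect at lower, more negative TP7–TP8.
- Name a TP7–TP8 imbalance outcome alongside left β/θ and right β/θ, since Expected Results places the interaction on bilateral imbalance.
- For these three outcomes, add the continuous screening score and the Phase × Condition × score term. The same question can be put as Condition × score in a model of change, or of post adjusted for pre.
- Report the slope difference between arms with a 95% CI, labelled exploratory, and say that the 0.87 power does not apply to it.

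The cost is a few sentences and a few degrees of freedom (error df 38 to 36 in the change model). The score is already to be collected. The downside is an imprecise interaction estimate with 40 participants, which is why it should be reported as an estimate with its interval and not as a confirmatory test. The changes should be made before any analysis by arm.

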## Discussion

Despite the current limited number of NF protocols for DD, previous evidence showed promising effects of NF training in inducing beneficial changes in reading-related functions (Breteler et al., 2012; Au et al., 2014; Sadeghi and Nazari, 2015; Eroğlu et al., 2020). To date, no previous study investigated a bilateral NF intervention targeting TP activation. Such novel bilateral NF intervention was adapted from effective NIBS studies (Turkeltaub et al., 2012; Costanzo et al., 2016a,b; Younger et al., 2016).

As compared to NIBS, NF has fewer exclusion criteria (Marzbani et al., 2016) and it is commonly used on neurodevelopmental disorders across the lifespan in clinical settings (e.g., on ADHD patients; Holtmann et al., 2014), fewer concerns about safety and ethical matters. Therefore, bilateral NF could be a more easily applicable neuromodulatory option for both younger and older individuals with DD.

In addition to proposing a novel NF intervention protocol, the present study protocol introduces a methodological advantage, namely, a placebo NF condition. Differently than previous NF experiments which used no-training control conditions in which participants were just resting, with this protocol we will propose a more controlled placebo condition where participants from both groups will receive the same instructions and the same visual experience. Indeed, the only difference will rely on the fact that the videogame would not be linked to the brain activities of control participants, as already proposed by other authors (Egner et al., 2002; Ros et al., 2013; Hosseini et al., 2016; Agnoli et al., 2018). This procedure will prevent some confounding effects related to unbalanced conditions in terms of cognitive effort, visual-perceptual stimulation, and motivation. Also, in this protocol, we opted for a single fake video (placebo) for all control participants to limit further confounding effects related to inter-subjective variability. Furthermore, compared to an alternative NF protocol (e.g., targeting different power frequencies and/or different brain regions), the placebo NF could help isolate the specific effect of the experimental NF mechanisms, and thus draw clear conclusions about its functional effect.

Another methodological novelty of the present protocol is the use of the β/θ power ratio in NF intervention for DD to suppress the θ activity and enhancing the β activity in the left TP regions while enhancing the θ/β power ratio in the less involved right TP regions during reading. The θ/β power ratio (Lubar, 1991) was considered based on its functional relevance as a marker of central nervous system arousal (Mann et al., 1992) and its prognostic value for neurodevelopmental disorders (Arns et al., 2013), as demonstrated by numerous findings on effective θ/β NF training in ADHD (Holtmann et al., 2014). The use of power-ratio metrics could be potentially associated with confounds and difficulties in their interpretations, as changes in ratio could stem from changes in any of the frequency bands. Furthermore, β and θ changes following NF are not always consistent (Janssen et al., 2017). To avoid this potential issue, each frequency band will be separately evaluated during the training periods, to extract the key driver of the ratio modulation effect.

As for the NF game selection, we opted for gameplay consisting of a matrix of visual stimuli (i.e., balloons) exploding sequentially from left to right, thus mirroring the typical visual scanning required during reading tasks. We hypothesize that such eye movements during the NF training would produce a matching neuropsychological condition that would facilitate the modulation of the reading-related TP imbalance.

Another important issue to discuss refers to our choice to use a single session in the light of conventional NF training studies, which include many consecutive sessions. Indeed, although the presence of positive effects has been mainly reported for longer protocols, the present single-session protocol aimed to propose a theoretical and practical model for NF interventions in DD to test whether a one-shot training could be sufficient to obtain some observable improvement on the behavioral but, above all, on the neurophysiological level. If so, the results could provide further information to plan longer-term sessions. Thus, our protocol explores the feasibility to target a well-known neurofunctional model, which, however, is rather neglected by the NF literature. Also, the clinical implications of such intervention will be taken into account for further developments.

A limitation of the present study protocol is the use of a low-resolution two-channel EEG. This EEG setup was selected, instead of a higher-resolution setup, for both practical reasons (it is the equipment which is most widely used to deliver treatments), and for studying the specific locations which are the object of the present protocol, namely bilateral TP, which are particularly relevant for DD neurofunctional basis.

Despite the discussed limitations, the present study protocol would be the first attempt to adapt the neuromodulation hypothesis of DD for NF training by testing both the feasibility and efficacy of a novel rehabilitation procedure for DD, and would finally lay the groundwork for future NF applications for DD.

## Ethics Statement

Ethical approval was obtained by the Psychology Research Ethics Committee of the Università Cattolica del Sacro Cuore, Milan, Italy on the 22nd January 2021 (Approval Numbers: 11-21). Participants will provide their written informed consent to participate in the study.
